## Abstract

**Background:**

Rapid treatment of stroke improves outcomes, but accurate early recognition can be challenging. Between 20 and 40% of patients suspected to have stroke by ambulance and emergency department staff later receive a non-stroke ‘mimic’ diagnosis after stroke specialist investigation. This early diagnostic uncertainty results in displacement of mimic patients from more appropriate services, inappropriate demands on stroke specialist resources and delayed access to specialist therapies for stroke patients. Blood purine concentrations rise rapidly during hypoxic tissue injury, which is a key mechanism of damage during acute stroke but is not typical in mimic conditions. A portable point of care fingerprick test has been developed to measure blood purine concentration which could be used to triage patients experiencing suspected stroke symptoms into those likely to have a non-stroke mimic condition and those likely to have true stroke. This study is evaluating test performance for identification of stroke mimic conditions.

**Methods:**

Design: prospective observational cohort study

Setting: regional UK ambulance and acute stroke services

Participants: a convenience series of two populations will be tested: adults with a label of suspected stroke assigned (and tested) by attending ambulance personnel and adults with a label of suspected stroke assigned at hospital (who have not been tested by ambulance staff).

Index test: SMARTChip Purine assay

Reference standard tests: expert clinician opinion informed by brain imaging and/or other investigations will assign the following diagnoses which constitute the suspected stroke population: ischaemic stroke, haemorrhagic stroke, TIA and stroke mimic conditions.

Sample size: ambulance population (powered for mimic sensitivity) 935 participants; hospital population (powered for mimic specificity) 377 participants.

Analyses: area under the receiver operating curve (ROC) and optimal sensitivity, specificity, and negative and positive predictive values for identification of mimic conditions. Optimal threshold for the ambulance population will maximise sensitivity, minimum 80%, and aim to keep specificity above 70%. Optimal threshold for the hospital population will maximise specificity, minimum 80%, and aim to keep sensitivity above 70%.

**Discussion:**

The results from this study will determine how accurately the SMARTChip purine assay test can identify stroke mimic conditions within the suspected stroke population. If acceptable performance is confirmed, deployment of the test in ambulances or emergency departments could enable more appropriate direction of patients to stroke or non-stroke services.

**Trial registration:**

Registered with ISRCTN (identifier: ISRCTN22323981) on 13/02/2019 http://www.isrctn.com/ISRCTN22323981

## Background

In the UK, stroke is the third leading cause of death and the single largest cause of adult disability with an overall economic impact of approximately £9 billion per year [1]. The cause of stroke is either cerebral ischaemia (85%) or haemorrhage (15%), and evidence of cost-effective disability reduction exists for early access to specialist services (all patients: NNT 20) [2], intravenous thrombolysis (IVT) for ischaemic stroke <4.5 h since onset (10–15% patients: mean NNT 7) [3, 4] and intra-arterial mechanical thrombectomy (MT) for large vessel occlusion stroke (LVO) < 6h since onset (5–10% patients: NNT 3) [5]. To improve access to treatments, national policy is driving the creation of regional neuroscience centres (also called comprehensive stroke centres) with thrombectomy capability or hyperacute stroke units (HASU; also known as primary stroke centres) which deliver thrombolysis and provide stroke unit care [6]. Increasing numbers of patients with suspected stroke are being redirected past the nearest hospital in order to access specialist care. Although outcomes are best when stroke patients are treated rapidly in a HASU or regional neuroscience centre, the emergency care pathway for admission is inefficient because accurate initial diagnosis is often difficult.

Ambulance practitioners, as the first point of contact in the clinical pathway for the majority of suspected stroke admissions, use a validated assessment to identify stroke symptoms and make a decision about where to take the patient [7]. Clinical guidelines specify that any suspected stroke should be conveyed directly to the nearest specialist stroke care centre [7]. The most widely used assessment is the Face Arm Speech Test (FAST), which records facial weakness, arm weakness and/or speech disturbance [8]. Although FAST has good sensitivity, poorer specificity results in 30–50% of ‘FAST positive’ patients later receiving a non-stroke ‘mimic’ diagnosis (i.e. false positives) [8, 9]. At hospital emergency departments, emergency medical staff can quickly identify more non-stroke mimic conditions during clinical assessment than ambulance practitioners, but the mimic rate is still 20–30% [10] resulting in frequent referral of mimics to stroke units rather than to appropriate alternative services according to the underlying condition.

This early diagnostic uncertainty can therefore result in displacement of mimic patients from more appropriate local hospitals or medical specialties within a hospital, inappropriate demands on finite stroke specialist resources and delayed access to specialist care and time-critical reperfusion therapies for true stroke patients. For example, national audit in England consistently shows that 44% of confirmed stroke patients are not admitted to a HASU within 4 h of hospital arrival [11], and as it has been observed that 15–20% HASU beds are occupied by patients with mimic conditions for a typical stay of 2.5 days [12], one explanation for the inability to achieve stroke service standards is the impact of ‘false positive’ stroke admissions (i.e. mimics) upon finite specialist resources.

Blood biomarkers have potential advantages in emergency assessment but have not previously proven useful during the critical early stages of stroke as release occurs hours after onset, and complex assays are required [13–15]. However, evidence is now accumulating that detection of whole blood purine concentration (WBPC) may be able to assist with stroke versus mimic identification [16–19]. Purines are short half-life natural by-products from energy-producing metabolic pathways which accumulate rapidly during hypoxic tissue injury [16]. Hypoxia is a main pathophysiological mechanism when stroke is caused by ischaemia (due to arterial occlusion) or haemorrhage (due to associated pressure effects and vasoconstriction), but for most common mimic conditions, significant tissue hypoxia is not involved (e.g. migraine). Whilst purines are not a tissue-specific biomarker and are elevated in other hypoxic states, cerebral tissue is a particularly rich source because of its high metabolic activity and oxygen sensitivity. In the clinical context of suspected stroke, a significant WBPC difference is expected between common mimic conditions (low WBPC values) and true stroke (higher WBPC values).

A portable point of care novel biosensor assay ‘SMARTChip Purine’ has been developed to measure WBPC from a fingerprick drop of capillary blood [19]. The assay consists of enzymatic biosensors printed within a strip of carbon substrate and a bespoke reader device. A coupled cascade of three enzymes (adenosine deaminase, purine nucleoside phosphorylase and xanthine oxidase) quickly detects the combined concentrations of purine: adenosine, inosine and hypoxanthine [17]. Figure 1 shows the SMARTChip technology.

**Fig. 1 Fig1:**
[figure not shown]
SMARTChip technology

The SMARTChip assay could be used to triage patients with suspected stroke symptoms into those people likely to have a non-stroke mimic condition and those likely to have true stroke. The assay may have maximum impact if deployed pre-hospital but may also be of use on arrival at hospital for patients who do not present to the ambulance service, or if the technology is not available in the ambulance or was not deployed by ambulance practitioners because stroke was not suspected. In both settings, the assay result would be useful for determining whether patients with suspected stroke symptoms continue along the stroke emergency assessment pathway or whether they should be directed to other more appropriate emergency services for further assessment and treatment (i.e. the test result indicates that a patient is likely to have a non-stroke mimic condition).

The SMARTChip assay may also have an alternative purpose in the context of suspected stroke. Due to the greater volume of brain tissue involved during LVO stroke, it is hypothesised that WBPC readings will be elevated higher and for a longer time period when compared to both mimic conditions and those stroke patients without LVO. Sequential SMARTChip assay readings may therefore be able to assist in identification of patients with LVO stroke. As time-critical mechanical thrombectomy treatment is only available in a small number of regional neuroscience centres (comprehensive stroke centres), patients with LVO suitable for thrombectomy typically require secondary transfer from a HASU. Rapid identification of mechanical thrombectomy-eligible patients could facilitate transfer and expedite access to treatment.

The main aim of this study is to evaluate the diagnostic accuracy of the SMARTChip assay for identification of stroke mimic conditions amongst the suspected stroke population when used in either the pre-hospital or hospital environment. An exploratory substudy will be conducted to assess whether serial WBPC values could be useful for the identification of LVO stroke.

## Methods

### Study objectives

To determine the diagnostic accuracy of SMARTChip assay WBPC readings for identification of stroke mimic conditions when a reading is obtained in the pre-hospital setting, i.e. the test is conducted on patients suspected to have stroke by ambulance staffTo determine the diagnostic accuracy of SMARTChip assay WBPC readings for identification of stroke mimic conditions when a reading is obtained in hospital, i.e. the test is conducted on patients suspected to have stroke by hospital staff and when an ambulance test has not been undertakenTo develop pre-hospital and hospital statistical models which combine routinely available clinical data with SMARTChip assay WBPC readings to predict a stroke mimic diagnosisTo prospectively determine the diagnostic accuracy of the statistical models from objective 3To report the failure rate of the SMARTChip assay when used in the pre-hospital and hospital settings

#### Substudy

To explore the diagnostic accuracy of two sequential SMARTChip assay WBPC readings for identification of LVO stroke using a reading obtained in the pre-hospital setting and a second reading obtained in the hospital settingTo develop and retrospectively explore the diagnostic accuracy of a statistical model which combines routinely available clinical data with pre-hospital- and hospital-obtained SMARTChip WBPC readings to predict the presence of LVO

### Study design

Two prospective blinded observational cohort studies will be conducted, one involving a convenience series of suspected stroke patients tested by hospital services and one involving a convenience series of suspected stroke patients tested by ambulance services. There will be 5 phases:
Phase 1: pilot cohort study in hospital to review key technical performance parameters of the SMARTChip assayPhase 2: main hospital cohort study part 1. Once agreement is reached that technical performance is satisfactory, data will be collected to determine the diagnostic accuracy of WBPC assay readings for identification of mimic conditions (objective 2) and to build the statistical model (objective 3).Phase 3: main hospital cohort study part 2. Data will be prospectively collected to confirm the diagnostic accuracy of (i.e. validate) the hospital statistical model (objective 4).Phase 4: ambulance cohort study part 1. Data will be collected to determine the diagnostic accuracy of WBPC assay readings for identification of mimic conditions (objective 1) and to build the statistical model (objective 3).Phase 5: ambulance cohort study part 2. Data will be prospectively collected to confirm the diagnostic accuracy of (i.e. validate) the ambulance statistical model (objective 4).

Phases 4 and 5 may overlap with phases 2 and 3 depending on logistical factors, e.g. time taken to commence ambulance service involvement or availability of sufficient testing equipment.

Data collection to report the failure rate of the SMARTChip assay will run across phases 2–5. Data collection for the substudy is relevant to phases 4 and 5 only.

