#### Statistical analyses

Objective 1: to determine the diagnostic accuracy of SMARTChip assay WBPC readings for identification of stroke mimic conditions when a reading is obtained in the pre-hospital setting, i.e. the test is conducted on patients suspected to have stroke by ambulance staff

For the PP group, logistic regression analyses with binary diagnosis of mimic or stroke (with TIA grouped with stroke as the intended purpose of the test is to identify mimic) as the outcome variable and WBPC reading as the explanatory variable will be used to construct a receiver operating curve (ROC) for all possible test thresholds. Area under the ROC curve and optimal sensitivity, specificity, and negative and positive predictive values, will be reported with 95% confidence intervals (CI). Optimal thresholds for sensitivity and specificity will be chosen. As we consider that test sensitivity is more important than specificity in the ambulance, the optimal threshold will be chosen to maximise sensitivity for mimics, minimum 80%, but aiming to keep estimated specificity for mimics above 70%. At lower levels of sensitivity and specificity, the test is unlikely to be considered of value.

For the ITT group, sensitivity and specificity will be calculated using a two-by-two table. Patients with a verified WBPC reading will be assigned a ‘test diagnosis’ according to the optimal threshold established in the PP analysis, and patients with an unverified WBPC will be assigned a test diagnosis of stroke. If the SMARTChip was deployed in clinical practice and an unverified reading was obtained, patients would continue to be managed as suspected stroke as there would be no extra information to exclude this possibility.
2.Objective 2: to determine the diagnostic accuracy of SMARTChip assay WBPC readings for identification of stroke mimic conditions when a reading is obtained in hospital, i.e. the test is conducted on patients suspected to have stroke by hospital staff and when an ambulance test has not been undertaken

For this objective, analyses as described above for objective 1 will be conducted. In terms of optimal thresholds, as we consider that test specificity is more important than sensitivity in hospital, the optimal threshold will be chosen to maximise specificity for mimics, minimum 80%, but aiming to keep estimated sensitivity for mimics above 70%. At lower levels of specificity and sensitivity, the test is unlikely to be considered of value.

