3.Objective 3: to develop pre-hospital and hospital statistical models which combine routinely available clinical data with SMARTChip assay WBPC readings to predict a stroke mimic diagnosis

Key variables will be added to the PP models described above to determine if this could significantly increase their accuracy. Clinical variables that would be available to ambulance/hospital staff will be included to reflect those available at the point of testing. Stepwise regression with backward elimination will be used to select the clinical covariates that most influence the diagnosis of mimics in conjunction with the WBPC readings.

A stepwise variable selection procedure will be used, and only variables that significantly improve the AIC will be retained in the model. Sensitivity, specificity, ROC AUC (with confidence intervals) and threshold will be reported if a suitable model is found.
4.Objective 4: to prospectively determine the diagnostic accuracy of the statistical models from objective 3

The models derived under objective 3 will be used to predict mimic/stroke status, and sensitivity, specificity and negative and positive predictive values will be reported with 95% confidence intervals (CI) for the PP population.
5.Objective 5: to report the failure rate of the SMARTChip assay when used in the pre-hospital and hospital settings

Reasons why a SMARTChip assay measurement was attempted but not obtained will be categorised and reported. This will include the following:
Failed SMARTChip calibration or bufferFailed SMARTChip reading following successful calibration (i.e. unverified reading)User-reported clinical or operational reason for aborting the calibration or reading process

A failure rate will be calculated for pre-hospital and hospital settings.
6.Subgroup and exploratory analyses

Diagnosis accuracy calculations will be performed on a pre-specified subgroup of the PP population consisting of only those patients with a reference standard diagnosis of ‘Definite Stroke’ and ‘Definite Mimic’ (this subgroup analysis is being undertaken as it considers the highest level of clinical confidence in the diagnosis and therefore allows exploration of the SMARTChip assay performance under ideal conditions). Contingent on the results of the study, it may be important to carry out some data-driven exploratory analyses. These will be determined post hoc and reported as such.
7.Substudy analysis

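### The combined models' only planned AUC comes from the patients used to select them, and no phase gives these models an intention-to-test result

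*Protocol article*

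**What the plan says.** All references are to the protocol article. Under Study design, phases 2 and 4 supply the data that build the hospital and ambulance models, and phases 3 and 5 validate them. For phase 3: "Data will be prospectively collected to confirm the diagnostic accuracy of (i.e. validate) the hospital statistical model (objective 4").

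Under Statistical analyses, the measures differ by objective:

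- **Objectives 1 and 2 (WBPC alone):** "Area under the ROC curve and optimal sensitivity, specificity, and negative and positive predictive values, will be reported with 95% confidence intervals (CI"). There is also an ITT analysis: "For the ITT group, sensitivity and specificity will be calculated using a two-by-two table". In that table an unverified reading counts as a test result of stroke, because in practice such a patient would stay on the stroke pathway.
- **Objective 3 (combined models, development):** "Key variables will be added to the PP models described above to determine if this could significantly increase their accuracy". Selection is stepwise: "Stepwise regression with backward elimination will be used to select the clinical covariates that most influence the diagnosis of mimics". The output is: "Sensitivity, specificity, ROC AUC (with confidence intervals) and threshold will be reported if a suitable model is found". No correction for optimism is stated.
- **Objective 4 (combined models, validation):** "sensitivity, specificity and negative and positive predictive values will be reported with 95% confidence intervals (CI) for the PP population".

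The abstract puts AUC first among the accuracy measures: "area under the receiver operating curve (ROC) and optimal sensitivity, specificity, and negative and positive predictive values for identification of mimic conditions".

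**The concern.** Two things are missing at the stage where the combined models meet new patients.

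**AUC.** An AUC computed in the patients who determined which covariates stay and what their coefficients are is an apparent AUC, and on average it is too high. Phases 3 and 5 could supply an unbiased one, but objective 4 does not list it. At one fixed cut-off, a change in sensitivity and specificity between development and validation could be lost discrimination or only a shift along the ROC curve. Without an AUC the two cannot be told apart.

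**Unverified readings.** A combined model needs a WBPC reading. The reason given for counting unverified readings as stroke applies to it as much as to WBPC alone, yet neither objective 3 nor objective 4 carries an ITT table. A PP-only validation could look adequate while the same model, run under the plan's own rule, falls short of the plan's own minimum.

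**Working it through.** **Step 1: planned numbers (Sample size section).** The plan's figures reproduce.

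- Hospital: 125/0.75 = 166.7, so 167; 100/0.75 = 133.3, so 134; 167 + 134 = 301; 301/0.8 = 376.25, so 377.
- Ambulance: 199/0.4 = 497.5, so 498; 100/0.4 = 250; 498 + 250 = 748; 748/0.8 = 935.
- Exact binomial power, one-sided 5%: 92.7% at 125 (0.80 v 0.90) and 92.2% at 199 (0.80 v 0.88).

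The group sizes used below are:

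| | Mimics | Non-mimics |
|---|---|---|
| Hospital development | 167 − 125 = 42 | 125 |
| Hospital validation | 134 − 100 = 34 | 100 |
| Ambulance development | 199 | 498 − 199 = 299 |
| Ambulance validation | 100 | 250 − 100 = 150 |

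**Step 2: optimism of the development AUC.** The article does not give the number of candidate variables, so 10, 20 and 30 are assumed. Two simulations used backward elimination on AIC with WBPC kept in the model and the remaining candidates as noise. Simulation A assumes that WBPC separates the groups by 1 SD, with four weak true predictors of 0.35 SD. Simulation B assumes a WBPC separation of 0.8 SD, with three weak true predictors of 0.3 to 0.4 SD. The table shows development AUC minus AUC in independent patients.

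| Candidates | Hospital A | Hospital B | Ambulance A | Ambulance B |
|---|---|---|---|---|
| 10 | 0.05 | 0.061 | 0.015 | 0.013 |
| 20 | 0.09 | 0.099 | 0.025 | 0.027 |
| 30 | 0.14 | 0.150 | 0.036 | 0.037 |

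For scale, with 20 hospital candidates in B the development AUC averaged 0.810 and the independent AUC 0.711.

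**Step 3: precision of a validation AUC.** Hanley-McNeil: SE² = [A(1−A) + (n₁−1)(Q₁−A²) + (n₂−1)(Q₂−A²)]/(n₁n₂), with Q₁ = A/(2−A) and Q₂ = 2A²/(1+A). At an assumed A = 0.80, Q₁ = 0.6667 and Q₂ = 0.7111.

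- Hospital: (0.16 + 33 × 0.02667 + 99 × 0.07111)/3400 = 0.002377; SE 0.0488; 95% half-width 0.096.
- Ambulance: (0.16 + 99 × 0.02667 + 149 × 0.07111)/15000 = 0.000893; SE 0.0299; half-width 0.059.

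For A from 0.75 to 0.90 the half-width runs from 0.10 to 0.07 in hospital and from 0.06 to 0.04 in the ambulance cohort.

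**Step 4: effect of the unverified-reading rule.** Let u be the share of unverified readings. Assume that u is the same in mimics and strokes, and that verified readings outside the PP group perform as those inside it. Then

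- ITT sensitivity = PP sensitivity × (1 − u)
- ITT specificity = 1 − (1 − PP specificity) × (1 − u)

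The article gives no value for u.

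| u | Ambulance sensitivity, 88% in PP | Hospital sensitivity, 70% in PP | Hospital specificity, 90% in PP |
|---|---|---|---|
| 5% | 83.6% | 66.5% | 90.5% |
| 10% | 79.2% | 63.0% | 91.0% |
| 20% | 70.4% | 56.0% | 92.0% |

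The 88% crosses the 80% minimum where 1 − u = 0.80/0.88 = 0.909, that is u ≈ 9.1%. The 88% and 90% are design values from the sample-size section, and the 80% and 70% are the threshold targets of objectives 1 and 2. All were set for WBPC alone and are borrowed here for the combined models. The 20% row is only an outer bound (see the objection).

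**The case against.** The best defence is that the article condenses a fuller protocol, an unseen SAP may add a validation AUC, and naming some measures does not exclude others. It is fair that nobody can say what will finally be published. But objective 4 is not silent: it lists its measures and restricts its population, and both are narrower than in the objectives around it.

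Other points stand and limit the concern:

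- **Decision measures are validated.** The plan judges usefulness by sensitivity and specificity, and objective 4 estimates both in new patients. Optimism in the AUC does not carry over to those estimates.
- **Failed readings are not ignored.** Objective 5 reports the failure rate by setting, with data from phases 2 to 5, so a reader could approximate ITT sensitivity with the formula above.
- **The AUC effect depends on assumptions.** It is small in the ambulance cohort. In hospital, optimism with 10 or 20 candidates is about the size of the validation AUC's own half-width or less. A validation AUC would therefore not prove optimism in a given dataset, but it would remove the bias from the quoted figure.

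Two stronger readings are tempting. A reader might infer that an ITT table for the combined models was planned and then removed at validation. The text does not support this: the table belongs to objectives 1 and 2, and objective 3 builds on PP models from the start. A reader might also take the 20% sample-size allowance as the unverified share. That allowance covers everyone outside the PP group, including ineligible patients and unclear diagnoses, and unclear diagnoses are excluded from ITT as well.

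**Conclusion.** The concern holds as a reporting gap that is worth closing. It does not invalidate any objective.

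Followed as written, the plan gives the combined models one AUC, an apparent one. Its expected excess is roughly 0.05 to 0.15 in hospital and 0.01 to 0.04 in the ambulance cohort, conditional on 10 to 30 candidates and the simulated effect sizes. The plan also gives these models no estimate under its own rule for unverified readings.

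The two parts bite in different places. The AUC matters mainly in hospital, where development rests on about 42 mimics. The ITT result matters most in the ambulance cohort, where sensitivity has a stated minimum: 88% in PP falls below 80% once u exceeds about 9%. In hospital the rule slightly raises specificity, the priority measure there, and lowers sensitivity. Whether u reaches 9% cannot be known from the article.

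**What to change.** In objective 4:

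1. State that the model and its threshold are frozen at the end of development and applied without refitting in phases 3 and 5. The article already says that the objective 3 models will be used for prediction, so this mainly makes the threshold explicit.
2. Report the validation AUC with its 95% CI, and quote it as the model's AUC in place of the objective 3 value.
3. Beside the PP results, add the ITT two-by-two table for the combined model, with unverified readings counted as stroke, as in objectives 1 and 2.

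Calibration intercept and slope are optional and can be left to the SAP.

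The cost is a few lines of text and code. The data are already to be collected and no sample size changes. The downside is slightly more analysis and, possibly, a lower reported AUC and sensitivity.
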